# **Informed Consent/Authorization**

Patients will have consented to participate in this study.

The informed consent will be obtained by the RELIEF study coordinator or one of the investigators of the study with a clear description of the purpose and procedures of the study, the implications for enrolled patients in terms of clinical care whether they decide to participate in the study or not, the potential risks and benefits of the study. It will be made clear to participants that they will be at liberty to withdraw from the study at any point or decline participation outright without influencing their level of clinical care. Oral and written consent will be obtained with the signed informed consent archived in the research department of the Division of Pulmonary & Critical Care at Vanderbilt University. The patient will be furnished with a copy of the signed study documents for his or her personal records.

# **Data Confidentiality and Monitoring**

Study data will be collected and managed using REDCap (Research Electronic Data Capture) electronic data capture tools hosted at Vanderbilt University. REDCap (www.project-redcap.org) is a secure, web-based application with controlled access designed to support data capture for research studies, providing: 1) an intuitive interface for validated data entry; 2) audit trails for tracking data manipulation and export procedures; 3) automated export procedures for seamless downloads to common statistical packages; and 4) procedures for importing data from external sources (Harris). In the case of multi-center studies, REDCap uses Data Access Groups (DAGs) to ensure that personnel at each institution are blinded to the data from other institutions.

Vanderbilt will have access to the data captured at the research sites and will use the data combined from all databases for complete analyses.

Following publication study data will be archived in REDCap. Since study data may be useful for future research studies performed under separate IRB-approved protocols, study data will be archived indefinitely in REDCap. Since REDCap is a secure electronic database with controlled access, and because patient identifiers may be needed to link study data to data from other sources under future IRB-approved protocols, patient identifying information will be retained in the archived database.

# **Safety**

We do not expect additional safety concerns from this protocol over those incurred during conventional placement and maintenance of chest tubes. These risks, inherent to the chest tube procedure itself, are discussed as part of the clinical informed consent and include bleeding, infection, pain, and pneumothorax. No interventions outside the standard of care of performed in this study.

*Adverse event (AE)*

An adverse event (AE) is any untoward medical occurrence in a patient administered a pharmaceutical product, which does not necessarily have a causal relationship with the treatment. This study is expected to have minimal to no adverse effects.

Treatment-related adverse events will be collected for this study. Therefore, data, including adverse events, will be collected from patients pre- or post-treatment. Only adverse events related to research procedures (the consent process, pain assessment, HIPAA compliance, etc.) will be collected.

Serious adverse events will be recorded as part of the study.

*Serious adverse event (SAE)*

This study will not have any serious adverse effects. A serious adverse event (SAE) is an undesirable sign, symptom, or medical condition which:

- is fatal or life-threatening.
- requires or prolongs inpatient hospitalization.
- results in persistent or significant disability/incapacity.
- jeopardizes the participant and requires medical or surgical intervention to prevent one of the outcomes listed above.

Events not considered to be serious adverse events are hospitalizations for:

- Routine treatment or monitoring of the studied indication, not associated with any deterioration in condition, or for elective procedures.
- Elective or pre-planned treatment for a pre-existing condition that did not worsen.
- Emergency outpatient treatment for an event not fulfilling the serious criteria outlined above cannot resulting in inpatient admission.
- Respite care.

General Instructions for Reporting Serious Adverse Events

The Institutional Review Board will be notified of all SAEs, within 7 business days after the treating institution becomes aware of the event. Only SAEs related to research procedures will be reported to the IRB.

*Benefits*There is no guarantee that the subjects will receive any benefit from this study.

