**Table 2. Imaging data collected on day of chest drain removal**

| **Day of Chest Drain Removal: Effusion Classification** |
| --- |
| **Chest X-Ray** |
| 0= no pleural fluid present  1= blunting of the costophrenic angle  2= fluid occupying up to 25% of the hemithorax  3= fluid occupying between 26-50% of the hemithorax  4= fluid occupying between 51-75% of the hemithorax  5= fluid occupying between 76-100% of the hemithorax |
| **Ultrasound** |
| Number of rib spaces occupied by effusion in the:  -Anterior view (#)  -Axillary view (#)  -Posterior view (#) |
| **CT Scan** |
| Effusion characteristics:  -Presence or absence of loculations  Effusion size in non-loculated effusion:  - Scant volume/small  - ≤ 1/4 of hemithorax  - ¼ to ≤½ of hemithorax  - ½ to ≤ 3/4 of hemithorax  - ¾ to almost entire hemithorax |

12) Follow up-Data

1. Other treatment strategies: including presence of additional chest tube in the same pleural space, surgical consult (and if applicable surgery date and interventions).
2. Post hospitalization data: Including date of discharge, status of empyema 4-6 weeks and 3 months after removal, and date of infection resolution on chest imaging
3. Complications: Including procedural and treatment related complications, or study-related complications
4. Patient status at follow-up: To further characterize patient outcomes following discharge after successful chest-tube removal, additional data will be collected regarding patient status at their follow-up visit and characterized based on five scenarios:
   1. Follow-up: resolved infection: Upon clinician follow-up there is no further evidence of residual infection clinically and on imaging and no further need for evaluation or treatment for infection resolution.
   2. Follow-up: surveillance: Upon clinician outpatient follow-up there is clinical concern for potential continued or residual infection despite initial chest tube drainage, requiring further clinical evaluation and potentially further procedures for resolution.
   3. Follow-up: ongoing infection: Upon clinical outpatient follow-up there is clear imaging or clinical signs of ongoing pleural infection despite initial chest tube drainage, actively requiring further management.
   4. Patient lost to follow-up: Following hospital discharge, the patient has been unable to be contacted or not presenting to outpatient appointments.

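### The Safety section gives incompatible rules for which adverse events are collected and which SAEs go to the IRB, and neither rule is tied to the Complications outcome

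*Protocol*

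**What the plan says.** The Safety section of the protocol makes these statements on adverse events:

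- It defines an adverse event as an occurrence "which does not necessarily have a causal relationship with the treatment".
- On collection it says "Treatment-related adverse events will be collected for this study".
- Two sentences later, in the same paragraph, it says "Only adverse events related to research procedures (the consent process, pain assessment, HIPAA compliance, etc.) will be collected".

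On serious events:

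- "Serious adverse events will be recorded as part of the study", with no relatedness condition in that sentence.
- "The Institutional Review Board will be notified of all SAEs, within 7 business days" of the site becoming aware.
- Directly after that, "Only SAEs related to research procedures will be reported to the IRB".
- The SAE subsection opens by asserting that the study will have no serious adverse effects.

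Elsewhere, Complications are secondary outcome 4 (Outcomes) and part of the secondary objective (Objectives; Statistical Considerations). The follow-up data list after Table 2 (Data Collection) has the item "Complications: Including procedural and treatment related complications, or study-related complications". The analysis plans under Statistical Considerations give complications by treatment as an example for the chi-square or Fisher's exact test.

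**The concern.** A site needs one answer to two questions: which events to write down, and which serious events to send to the IRB. The protocol gives two answers to each.

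This matters beyond tidy wording because complications are compared between arms. If one site follows the restrictive sentence and another follows the treatment-related one, the adverse event data will not mean the same thing across sites. If events enter the record only after someone judges them related, the count depends partly on that judgement, and in this open-label trial the person judging knows the arm. The trial's safety statement on regular flushing would then rest on data whose collection rule cannot be stated.

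**Working it through.** No figure in the protocol bears on this point: it gives no adverse event or complication rate. The check is therefore a comparison of the text.

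**1. Adverse event collection.** One sentence includes treatment-related events. The later one begins with a word that excludes everything not related to research procedures, and its examples are the consent process, pain assessment and HIPAA compliance, none of which is the treatment. The second sentence cannot easily be read as explaining the first. The definition adds a further tension: it requires no causal link, while both collection sentences filter on one.

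**2. Does flushing count as a research procedure?** The protocol does not say. Scheduled flushing is what is randomised, which suggests yes. The Safety section says that nothing outside standard of care is done in the study, which suggests no.

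**3. What the restrictive sentence would exclude.** The Safety section names pneumothorax, bleeding, pain and infection as the risks and attributes them to the chest tube procedure itself. By that description they are not research-procedure events. All four would go unrecorded as adverse events under a literal reading.

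**4. SAE reporting.** Notifying the IRB of all SAEs and reporting only the research-related ones are different rules. For an unrelated SAE, the first requires a notice within 7 business days and the second requires none. Recording is not the problem here, since that sentence carries no filter.

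**5. Link to the outcome.** The follow-up data list collects procedural, treatment-related and study-related complications without restriction by arm. It does not say how this item relates to adverse events, or which rule prevails where they conflict. The daily checklist is described in Study Procedure as covering blockage and the continuing need for the tube; complications are not mentioned there.

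**6. Effect on the arms, by reading.**

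- *Literal reading of the restrictive sentence.* The examples apply equally to both arms, so collection is close to empty in both. There is no artificial difference, but almost no adverse event information either.
- *Treatment-related, with treatment meaning chest tube care.* Events can qualify in both arms, subject to unblinded judgement.
- *Treatment-related, with treatment meaning the scheduled flush.* Events can be attributed to it only in the flushing arm. Controls have no routine instillation, though they may be flushed with 20 mL when the tube is judged blocked. Ascertainment may then differ by arm.

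The text does not settle which of the three applies.

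**The case against.** The strongest reply is that the harm is limited because the protocol captures much of what matters by other routes. That is largely right. Complications have their own line in the follow-up data, and its procedural category covers chest-tube events without requiring attribution to the research. Catheter replacement after dislodgement or failure to drain is recorded (Data Collection, item 8). Removal for dislodgement, malposition or kinking, and death with the tube in place, are handled as competing risks (Statistical Considerations). Off-protocol flushes and daily blockage data are also collected. The case report form is not shown and may already carry a complication list.

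A reader might therefore infer too much in two ways:

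- *That ascertainment differs by arm.* The documents do not support this as a fact. The examples in the restrictive sentence are not specific to an arm, controls can receive as-needed flushes, and no passage sets different collection rules for the arms. It is a risk under one reading only. Any numerical illustration of an arm difference would assume that reading and a complication rate that the protocol does not give.
- *That the Complications outcome has no data, or cannot be estimated without bias.* The separate collection route rules out the first and leaves the second unproven.

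It can also be said that limited adverse event collection is a legitimate choice when two standard-of-care practices are compared, and that the second IRB sentence merely narrows the first. The choice is legitimate, but it has to be stated once. A narrowing sentence does not repair one that says all. These points reduce the consequence and leave the contradictions standing.

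**Conclusion.** The Safety section contradicts itself twice, on adverse event collection and on IRB notification of SAEs. Its restrictive collection sentence also conflicts with the Complications outcome, with the item that collects it and with its planned comparison by treatment. These are matters of wording and rest on no assumption.

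The consequence is moderate. The primary outcome is untouched and complications retain a separate collection route. What is at risk is a consistent adverse event record across sites and, if staff filter by relatedness to treatment, comparable ascertainment between arms. The latter is conditional: it assumes that treatment or research procedure is taken to mean the scheduled flush. The size cannot be quantified from the protocol.

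**What to change.** - Replace the restrictive collection sentence with one rule, applied identically in both arms from randomisation: chest-tube complications (at least the four risks named in the Safety section) and all SAEs are recorded regardless of attributed cause, with relatedness entered as a separate field.
- Bring the treatment-related sentence into line with that rule.
- State that these records feed secondary outcome 4 and the complications item in the follow-up data, and that the comparison by arm uses events irrespective of relatedness.
- Reconcile the two IRB sentences into a single reporting rule. Recording and reporting can have different scopes if each is stated once.
- Delete the sentence asserting in advance that the study will have no serious adverse effects.

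The cost is a protocol wording amendment and slightly more data entry, possibly a few fields on the existing daily form if the case report form does not already have them. Treatment of patients does not change.

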# **Finances**

*Payment and Remuneration*

Subjects will not be paid to participate in the study.

*Costs*

There will be no additional costs to subjects for participating in this study. Subjects and/or their insurance companies will be responsible for part of the care provided as this service is part of the standard of care they would receive for their condition.

*Budget*

Funding provided by Cook Medical Inc.

